### Follow-up

Acute toxicity will be scored conform previous studies (weekly during therapy, 10 days and 1 and 3 months after completing CRT) using a combination of RTOG supplemented with own grading for those toxicities not comprised in the RTOG scoring and CTCAE for hematologic toxicity [7, 17]. This will allow for matched-case comparison for acute toxicity with patients treated in previous studies [7, 17]. Chronic radiation toxicity (toxicity occurring > 3 months after completing CRT or acute toxicity lasting longer than 3 months) will be assessed at every follow-up visit conform previous studies [7, 17]. Again, this will allow for matched-case comparison for toxicity with patients treated in previous studies.

Local (LC), regional (RC) and distant control is defined as absence of disease at the primary tumor bed, the regional lymph nodes and distant sites respectively. Time to local relapse, regional relapse and distant relapse were defined as the time elapsed between biopsy and the first event (local, regional or distant relapse) or the last follow-up. PFS and OS were defined as the time elapsed between biopsy and any progression, death or the last follow-up.

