### Study objectives and endpoints

The objective of this study is to assess the safety of excluding the non-involved uterus from the TV in the definitive CRT treatment of LACC. The primary endpoint is absence of tumor in the non-involved (as determined on the pre-treatment MRI) and non-high doses irradiated part of the uterus in the hysterectomy specimen after CRT. Secondary endpoints include a dosimetric comparison of dose on the OARs when comparing study treatment plans to treatment of the whole uterus at high doses; acute and chronic toxicity, OS, local relapse free and progression free survival (PFS). A translational part of the study is discussed below.

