### Inclusion/exclusion criteria

Eligible patients suffer from biopsy proven carcinoma of the uterine cervix. Following inclusion criteria should be met: locally advanced disease (FIGO IB2 or > FIGO IIB or node positive) proven by clinical examination, 18-fluorodeoxyglucose positron emission tomography scan (^18^FDG PET-CT) and MRI; no more than 2 distant metastases (other than para-aortic or inguinal lymph nodes); WHO 0–2; adequate kidney function for cisplatin, in case of inadequate kidney function cisplatin can be replaced by 5-FU or radiotherapy can be the sole therapeutic regimen; not pregnant or breastfeeding; absence of any psychological, familial, sociological or geographical condition potentially hampering compliance with the study protocol and follow-up schedule; willing and able to sign a written informed consent. Patients unable to undergo MRI for any reason are excluded.

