### Statistical considerations

For the EXIT-trial; 21 patients are required to achieve a confidence interval with a half width of 11%, considering a negative predictive value of 98% for MRI [13] to predict absence of tumor (Wilson Score Confidence Interval for a Binomial Proportion). These patients will also be used for the observational CRIMP trial. For the plan comparison, statistics will be done using a paired T-test. All statistical analysis will be performed using SPSS.

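### OS is defined with the same events as PFS, and local relapse-free survival is listed as an endpoint but only a time to local relapse without death is defined

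*Protocol article*

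**What the plan says.** The section on study objectives and endpoints names the secondary clinical outcomes as "acute and chronic toxicity, OS, local relapse free and progression free survival (PFS". The Methods part of the Abstract gives the same three survival-type endpoints. OS, local relapse-free survival and PFS are therefore meant to be three different quantities.

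The definitions are in the Follow-up section.

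- PFS and OS share one sentence: "PFS and OS were defined as the time elapsed between biopsy and any progression, death or the last follow-up".
- Relapse times, separately named for local, regional and distant relapse, are "the time elapsed between biopsy and the first event (local, regional or distant relapse) or the last follow-up". Death is not mentioned.
- The control states are defined just before: "distant control is defined as absence of disease at the primary tumor bed, the regional lymph nodes and distant sites respectively".

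No section defines local relapse-free survival under that name. The section on statistical considerations names no estimator for any time-to-event outcome. Its one design figure concerns the primary endpoint: "21 patients are required to achieve a confidence interval with a half width of 11%, considering a negative predictive value of 98% for MRI".

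**The concern.** A definition of OS that ends at progression does not measure overall survival. An analyst who followed the sentence would report one curve under two names and would have no analysis of mortality. A reader comparing that OS with other series would be comparing a progression-or-death outcome with a death outcome.

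For local relapse-free survival, the name implies that a patient who dies without local relapse has had an event. The only definition offered does not count that death. Depending on which text the analyst follows, the same patient is either an event or not. This matters because the trial's stated objective is the safety of leaving uninvolved uterus out of the target volume, and local relapse is a direct clinical check on that.

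**Working it through.** **1. The plan's own figure.** None is attached to the survival definitions. The only design figure is n = 21 for the primary endpoint, based on the "Wilson Score Confidence Interval for a Binomial Proportion". With p = 0.98, n = 21 and an assumed two-sided 95% level, the plain Wilson interval is 0.813 to 0.998 (half width 9.2%). The continuity-corrected version is 0.779 to 1.000 (half width 11.1%), which matches the stated 11%. OS, PFS and local relapse do not enter this calculation, so what follows leaves n = 21 untouched.

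**2. The OS/PFS sentence under each possible reading.**

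| Reading | PFS ends at | OS ends at | Result |
|---|---|---|---|
| Literal: one event list for both | progression or death | progression or death | OS equals PFS |
| With *respectively* supplied | progression | death | death is missing from PFS |
| Conventional meaning | progression or death | death | needs two event lists; the sentence gives one |

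Neither grammatical reading gives the conventional pair. The same paragraph does use *respectively* for the control definitions, so its absence here cannot simply be assumed away.

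**3. Size of the literal reading (illustration only).** At a fixed time, let P be the proportion progressed, D the proportion dead, and s the share of deaths that follow progression. All three are assumed, because the documents give none of them.

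- Death-only OS = 1 − D
- Literal OS = 1 − [P + D(1 − s)]
- Gap = P − D·s, which is the proportion progressed but still alive

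| P | D | s | Death-only OS | Literal OS | Gap | Extra events, 21 × gap |
|---|---|---|---|---|---|---|
| 0.20 | 0.10 | 0.8 | 0.90 | 0.78 | 0.12 | 2.5 |
| 0.20 | 0.10 | 1.0 | 0.90 | 0.80 | 0.10 | 2.1 |
| 0.30 | 0.20 | 0.8 | 0.80 | 0.66 | 0.14 | 2.9 |
| 0.30 | 0.20 | 1.0 | 0.80 | 0.70 | 0.10 | 2.1 |
| 0.40 | 0.30 | 0.8 | 0.70 | 0.54 | 0.16 | 3.4 |
| 0.40 | 0.30 | 1.0 | 0.70 | 0.60 | 0.10 | 2.1 |

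The gap is 10 to 16 points, or about 2 to 3 events. These pairs all hold P ten points above D. If progression ran further ahead of death, the gap would be larger: P = 0.40 with D = 0.10 gives 0.40 − 0.08 = 0.32 at s = 0.8 and 0.40 − 0.10 = 0.30 at s = 1.0. The gap vanishes only when nobody is alive after progression.

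**4. Local relapse.** Set the listed endpoint beside the only definition.

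| Patient's course | Local relapse-free survival, as the name is usually read | Time to local relapse, as Follow-up defines it |
|---|---|---|
| Local relapse | event | event |
| Death without local relapse | event | not an event; handling not stated |
| Alive without local relapse | censored | censored at last follow-up |

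The two differ by exactly the deaths without local relapse. As a crude proportion, each such death moves the result by 1/21 = 4.8 points; with censoring the shift is not exactly that. If these deaths were censored and one minus the Kaplan–Meier estimate were read as relapse risk, that risk would be overstated. The document names no estimator, so this is conditional. The bracketed list of sites in the definition also leaves open whether each time stops at relapse of its own site or at the first relapse of any site.

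**The case against.** The strongest defence is that this is compressed wording in a journal article. OS and PFS are listed separately, every oncology analyst knows that OS ends at death, and OS is wrong only if someone actually counts progression. No hypothesis, decision rule or sample size rests on OS or PFS. Time to local relapse is a legitimate variable without death, and censoring and competing-risk rules commonly sit in an analysis plan that is not shown here.

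Much of this stands. The intended meaning of OS can probably be guessed, the outcomes are secondary, and the lack of a stated estimator is no fault. It does not remove the point, because the article does not leave these definitions to another document. It states them, and the stated OS rule is wrong as it reads. For local relapse-free survival the defence is stronger, since a fuller document might define it. Even so, the article lists one endpoint and defines a different one.

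Stronger readings are tempting, and the documents do not support them.

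- Eligibility allows "no more than 2 distant metastases (other than para-aortic or inguinal lymph nodes", and distant control means absence of distant disease. A reader might infer that patients with metastases at entry count as distant failures from day one, or compute a ceiling such as 19/21 = 90.5% if two were enrolled. No passage scores baseline disease as an event. The timed event is relapse, distant control is not a listed secondary endpoint, and the documents give no number of such patients and do not say that their metastases must persist. Applied at biopsy, the same literal reading would deny local control to every patient, so the control states are evidently meant for after treatment.
- A reader might also object to starting the clock at biopsy. That origin is stated openly, applies to all these times, and in a single-arm trial with no survival hypothesis creates no between-group bias. The interval from biopsy to treatment is not given, so its effect cannot be sized.

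**Conclusion.** The point holds for two secondary endpoints. OS as written has the same events as PFS, and local relapse-free survival is listed while only a time to local relapse without death is defined. The first rests on the text alone and needs no assumption. Its illustrated size of 10 to 16 points, about 2 to 3 events in 21 patients, depends wholly on the assumed and paired progression and death rates. The second is smaller: a mismatch between name and definition whose effect equals the number of deaths without local relapse, which is unknown. The primary endpoint, its interval and n = 21 do not change. The definitions should be corrected before the survival analyses are run; the design does not depend on them.

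**What to change.** Replace the shared sentence and add one definition, keeping biopsy as the origin:

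- **OS:** biopsy to death from any cause, censored at last follow-up.
- **PFS:** biopsy to first progression or death from any cause, censored at last follow-up.
- **Local relapse-free survival:** biopsy to local relapse or death, whichever comes first, censored at last follow-up. Alternatively, rename the listed endpoint time to local relapse and report it as cumulative incidence with death as a competing event.
- **Site of relapse:** say whether each relapse time is specific to its own site.

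At most, add a line saying how metastases present at baseline are counted when distant control is reported.

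The cost is a few lines of text. Treatment, sample size and primary analysis stay as they are, and the events needed (relapse, progression, death, last follow-up) are ones the current definitions already name.

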### Additional and translational research

#### Planning study

Per patient, two different treatment plans (prescribed on PTV and PTV_EXIT as described above) will be generated. The OARs are the same for both plans and include small intestine, rectum, sigmoid colon, bladder and bone marrow. Prescription details can be found in our previous work [7, 8]. Dose Volume Histograms (DVHs) for all OARs will be calculated and compared between the two treatment plans. Per OAR, fixed dose-volume points of clinical relevance (e.g. volume of small bowel receiving ≥45 Gy, as used in previous research [8]) will be used for statistical comparison.

#### Correlation of high-risk regions on IMaging (DW-MRI) with pathology and regression pattern analysis (CRIMP)

The same patients who are the subjects of the clinical study will also be the subjects of the CRIMP study. The MRI at fixed time points (see Fig. 1) will be supplemented with diffusion weighing (DW). DW provides information about the amount of random movement of water molecules in a tissue. In healthy tissues the water molecules move relatively unhindered but in cancer the motion is strongly inhibited. This is depicted on DW as a high signal intensity area on high-b-value images with a corresponding low apparent diffusion coefficient (ADC) [18]. The ultimate aim of the CRIMP study is the correlation of tumoral ADC-values of the different DW-MRI with the pathology in order to predict therapy resistance or response to CRT at an early stage or even before start. The response on treatment assessed with pathology will be divided into 3 categories: A) no residual tumor or microscopic tumor rest consisting of fibrosis containing foci of neoplastic cells (the presence of isolated tumor cells/nests will not be considered as residual disease), B) macroscopic (> 7 mm) tumor rest revealing obvious tumor mass but showing CRT response and C) neoplastic tissue without any effect of radiation or regression. A high Apparent Diffusion Coefficient (ADC)_mean_ and limited increase (< 15%) in ADC_mean_ value 2 weeks after start of CRT corresponds with impaired response and survival [19, 20]. We hypothesize this will also correlate with residual tumor (isolated tumor cells excluded) at the HRT specimen. Both ADC_mean_ and median increase in ADC_mean_ will be correlated with the same pathology categories as mentioned here above.

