**Methods:**

The EXIT-trial is a phase II, single arm study aimed at LACC patients. This study evaluates whether a MRI-based exclusion of the non-tumor-bearing parts of the uterus out of the target volume results in absence of tumor in the non-high doses irradiated part of the uterus in the hysterectomy specimen. Secondary endpoints include a dosimetric comparison of dose on normal tissue when comparing study treatment plans compared to treatment of the whole uterus at high doses; acute and chronic toxicity, overall survival, local relapse- and progression-free survival. In the translational part of the study, we will evaluate the hypothesis that the baseline apparent diffusion coefficient (ADC) values of diffusion weighted MRI and its evolution 2 weeks after start of CRT, for the whole tumor as well as for intra-tumoral regions, is prognostic for residual tumor on the hysterectomy specimen.

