At this moment, MRI is widely used for initial local staging and target/OAR delineation and also increasingly used for monitoring treatment response after CRT. However, the accuracy of conventional MRI techniques only (T2 sequences) is less than DW-imaging for monitoring treatment response [27, 28]. A clinical and iconographical complete response after CRT predicts a better outcome, whereas macroscopic residual disease at the HRT specimen is an adverse prognostic factor for survival [29]. Residual disease reflects radio-resistant tumor clones, which are more aggressive and eventually lead to cancer-related mortality. Overcoming this radioresistance with a more aggressive treatment and/or higher doses might improve outcome. However, not all tumors as well as not all intra-tumoral sub-regions require a more aggressive approach. Biological heterogeneity within a tumor is a well-recognized phenomenon, which critically influences treatment outcome [30]. Local failure is likely more adversely influenced by those at-risk sub-regions (tumor voxels) within the heterogeneous tumor, which possess unfavorable biological properties. Early assessment of tumor response and at-risk sub-regions would permit modification of strategy during therapy by escalating the dose on non-responsive regions within the tumor or de-escalating dose in responsive regions. In cervical cancer, several studies have shown the utility of DW-MRI in the prediction or monitoring of response to CRT or in the prediction of recurrent disease. DW-MRI can yield quantitative information by means of serial ADC-measurements [31]. Treatment-induced cell damage precedes morphological changes and is associated with increased ADC-values, which are reliable in predicting treatment response [27, 32]. Already 2 weeks after start of CRT, ADC_mean_ and the change in ADC_mean_ from the baseline correlate with the final MRI response [19, 33, 34] and with survival [20]. Liu et al. [33] found that also baseline ADC values are significantly lower for the patients achieving a complete radiological response than those achieving a partial response. Tumors with high baseline ADC are likely to be more necrotic than those with low baseline ADC, which in turn predicts poor outcomes related to hypoxia-mediated radio-resistance [35]. However, few tumors do not respond favorably to CRT despite having lower pretreatment ADC values [36]. This may be due to the fact that necrosis within a tumor is not always associated with a high ADC. In theory, coagulative necrosis without tumor cell liquefaction may not increase the ADC [36]. It is therefore essential to combine pretreatment ADC value with the change in this value after 2 weeks of treatment for response prediction. To date, studies have focused on ADC_mean_, based on a region of interest (ROI) defined as the whole tumor or on 1 slice of the whole tumor [37]. According to the above-mentioned findings, radioresistant regions within the tumor will have higher baseline ADC values [33] and less change in ADC at 2 weeks [19, 33, 34, 36]. We hypothesize that baseline ADC and its evolution 2 weeks [36] after start of CRT will correlate with tumor rest in the hysterectomy specimen and that future dose escalation to those “at-risk” regions within the GTV could reduce the amount of residual macroscopic disease. In this way, DW-MRI could be used for assessing early treatment response and functional tumor heterogeneity for a personalized cancer RT strategy.

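### CRIMP correlates ADC_mean and its increase with pathology without combining them, though the Discussion calls combining essential; a baseline effect alone can then pass for an early-change marker

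*Protocol article*

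**What the plan says.** The Abstract (Methods) gives the translational hypothesis: baseline ADC and its evolution 2 weeks into chemoradiotherapy "is prognostic for residual tumor on the hysterectomy specimen".

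The CRIMP section starts from earlier literature, in which a high ADC_mean and a "limited increase (< 15%) in ADC_mean_ value 2 weeks after start of CRT corresponds with impaired response and survival". It continues: "We hypothesize this will also correlate with residual tumor (isolated tumor cells excluded) at the HRT specimen". Pathology is graded in three categories, A to C. The analysis itself is one sentence: "Both ADC_mean_ and median increase in ADC_mean_ will be correlated with the same pathology categories as mentioned here above". It mentions no combined score, joint model or adjustment of one marker for the other.

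The Discussion first notes that some tumors respond poorly despite a low pretreatment ADC, and concludes: "It is therefore essential to combine pretreatment ADC value with the change in this value after 2 weeks of treatment for response prediction".

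Statistical considerations assigns the same 21 patients to CRIMP and names a test only for the plan comparison.

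**The concern.** The article states a requirement for response prediction and then states an analysis that does not meet it. This goes beyond detail that a condensed article may leave out, because the conflict lies between two things the article does say.

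It matters statistically because the two markers are not separate pieces of information. The increase is judged against a threshold in percent of baseline, so baseline ADC enters both. A baseline value that is high by measurement error or chance raises the first marker and lowers the second. The hypothesis expects that same pattern in resistant tumors. If only baseline carries information, a single-marker analysis of the change will often also come out positive, and two positive results look like two confirmations. The Discussion hopes to use early ADC change in future response-adapted radiotherapy, so whether the change adds anything to baseline is the question a reader will ask.

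**Working it through.** **Inputs from the article.** n = 21 (Statistical considerations); the increase measured relative to baseline, with 15% as the threshold (CRIMP section); expected direction high baseline and small increase (CRIMP section, Discussion). The figure of 21 comes from the main trial's Wilson interval. At an assumed 95% level, 20 of 21 tumor-free gives a half width of 10.9% and 19 of 20 gives 11.4%, so 21 agrees with the stated 11% on whole-number outcomes; putting 98% in directly gives 9.2%. Nothing below depends on that calculation.

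**Inputs assumed, because the article gives none.** ADC means and SDs, the baseline/week-2 correlation r, the residual-tumor fraction, the effect size, and two-sided 5% tests.

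**Step 1: how one baseline error moves both markers.** With assumed means of 0.95 at baseline and 1.20 at week 2, the increase is 1.20/0.95 − 1 = 26%. If baseline reads 0.15 too high (one assumed SD), it is 1.20/1.10 − 1 = 9%. The same error makes baseline look high and takes the increase below 15%.

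**Step 2: size of the coupling.** Let c_b and c_f be the coefficients of variation at baseline and week 2. To first order,

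corr(baseline, % change) = (r·c_f − c_b) / √(c_b² + c_f² − 2·r·c_b·c_f).

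- Equal coefficients of variation: this reduces to −√((1 − r)/2). For r = 0.2, 0.5 and 0.8 it gives −0.63, −0.50 and −0.32. Simulation gives the same values.
- Equal SDs of 0.12 with means 0.90 and 1.12: c_b = 0.133 and c_f = 0.107. For r = 0.3 the formula gives −0.70, and for r = 0.9 it gives −0.62. Simulation gives −0.70 and −0.61.

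The second setting keeps a strong coupling even at high r, because the relative spread is smaller at week 2 than at baseline.

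**Step 3: consequence when only baseline is related to residual tumor (simulated, n = 21).**

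| Setting (assumed) | r | % change significant, tested alone | Adjusted for baseline |
|---|---|---|---|
| Equal CVs, one third residual tumor, odds ratio 4 per SD | 0.2 | 24% | 3–4% |
| same | 0.5 | 15% | 3–4% |
| same | 0.8 | 8% | 3–4% |
| Equal SDs, 40% residual tumor, baseline difference 1.0 SD | 0.3 to 0.9 | 21–27% | 4–5% |
| Equal SDs, 40% residual tumor, baseline difference 1.3 SD | 0.3 to 0.9 | 31–42% | 4–5% |

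In the last two settings, both markers are significant together in 18% to 40% of trials, although the change adds nothing to baseline. A separate repeat of the first setting gave about 24%, 15% and 8% unadjusted and about 4% adjusted.

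**Step 4: no effect at all (equal-SD setting).** When baseline is significant by chance, the change is also significant in 18% to 27% of trials, against 5% if the markers were independent. At least one of the two is significant in 8.4% to 8.7%, slightly below the 9.75% for two independent tests (1 − 0.95²). The harm is therefore false corroboration and not an inflated chance of any error.

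**The case against.** **The article does not say separately.** True. The sentence before the analysis describes a joint pattern, and the Discussion shows the intent to combine. A joint analysis is not excluded; it is not stated either. The analysis sentence therefore needs to be brought into line with the Discussion.

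**An unadjusted positive result for the change is not false.** Also true. If baseline predicts outcome and the change is correlated with baseline, the change is associated with outcome. The result misleads only if read as information beyond baseline, and the article nowhere promises independence. This limits the point to interpretation, but the reading is a natural one when two markers are reported side by side.

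**The size rests on assumed inputs.** It does. With equal relative spread and r = 0.8 the excess is small (8%). The direction is the same in every setting.

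**Stronger readings that a reader might infer.** The aim sentence speaks of "correlation of tumoral ADC-values of the different DW-MRI with the pathology in order to predict therapy resistance or response to CRT", and the imaging section lists five in-vivo scans, so one might count five or more tests and compute a large family-wise error rate. The documents do not support this. The aim sentence goes on to confine prediction to an early stage or before treatment starts. The hypothesis names only baseline and 2 weeks, and the two supplemental scans are given other purposes (regression-pattern analysis and the mold). One might also fault the lack of a single deciding contrast or of an exploratory label. In an observational sub-study reported in a condensed article, that is detail which may sit elsewhere. Requiring one joint two-degree-of-freedom test would also be a debatable trade: with about 7 residual tumors in 21 patients, simulated power for a baseline effect of odds ratio 4 per SD falls from about 65% to about 52%.

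**Conclusion.** The point holds in a limited form. The CRIMP analysis sentence does not carry out what the Discussion calls essential. Because the increase is relative to baseline, a baseline effect alone can make the 2-week change look like a second marker. Under the assumed inputs this happens in roughly 8% to 42% of trials of 21 patients, against about 3% to 5% with adjustment for baseline. The range reflects the unknown baseline/week-2 correlation, relative spread, effect size and residual-tumor fraction.

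The source of the coupling is shared baseline error and regression to the mean, not a change of scanner: Table 1 gives the same 1.5 T protocol for the scans before and during treatment. No patient's treatment in this trial depends on CRIMP, and neither the primary endpoint nor the 21 patients is affected. It is a cheap correction worth making before results are reported.

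**What to change.** In the CRIMP section, add to the analysis sentence:

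- One analysis of the pathology outcome with baseline ADC_mean and 2-week change entered together, for example penalised or exact logistic regression for residual tumor. Name the split of the stated categories, such as B or C against A.
- A statement that added value for the 2-week change will be claimed only from its baseline-adjusted estimate, reported with its confidence interval.
- A statement that the single-marker correlations are descriptive.

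The cost is a few sentences. No new patients, scans or measurements are needed, since both values are already collected. The downside is a wider interval for the change with 21 patients and some loss of detail if the three categories are reduced to two. The single-marker correlations with A, B and C would still show that detail.
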